#### Retention

Upon recruitment, a research assistant will conduct weekly follow-ups to remind the participant of upcoming doctor/data collection appointments and the recording of any adverse drug effects.

### Statistical analysis

#### Sample size calculation

PASS software version 11.0 (NCSS, LLC. Kaysville, Utah, USA) will be used to calculate sample sizes for both groups. Two recent studies conducted in China report that the clinical pregnancy rates of POR patients receiving DKP treatment and undergoing conventional IVF or ICSI based on a micro-stimulation protocol are 39.62 and 20.93%, respectively [13, 14]. In the present study, the clinical pregnancy rate in the DKP group is hypothesized to be 0.4 based on the null hypothesis and 0.25 on the alternative hypothesis. The clinical pregnancy rate in the placebo group is hypothesized to be 0.25. The test statistic used is the two-sided *Z* test with pooled variance. The significance level of the test targeted is 0.05. The ratio between groups will be 1:1. The minimum sample size for each group will be 203; hence, a total of 406 participants will achieve 90% power to detect a difference between the group proportions of 0.15. Assuming that the dropout rate of study participants is 10%, we expect to recruit 460 participants, with 230 participants in each group.

#### Randomization and allocation concealment

Patients will be randomly divided into two groups (1:1 ratio) using computer-generated random numbers managed by the Integrative Medicine team. CARDS identifying the DKP group and the placebo group will be placed in sealed, opaque envelopes and distributed by designated professional managers. Both medications (DKP formula and placebo) will be prepared in a manner that they will appear similar in appearance, flavor, and smell. Blinding of the clinicians, patients, and outcome and data analysts will be done. To ensure high accuracy, the trial will follow the updated guidelines from the Consolidated Standards of Reporting Trials (CONSORT) 2010 Statement [18] and the SPIRIT-TCM Extension 2018 for reporting of parallel-group randomized clinical trials [19]. Un-blinding will only occur in exceptional circumstances when matters cannot be resolved with ongoing randomization, and this will be performed by an authorized investigator. All un-blinding events will be reported and their reasons are given on the corresponding CRF.

#### Data management

Upon meeting the inclusion criteria, patients will be informed of the project objectives by the reproductive medicine practitioner and presented with informed consent. The patient’s demographic information will be recorded on the CRF. Any errors will be crossed, corrected, and signed by the corresponding investigator. CRF data will be entered and coded to a corresponding e-CRF using the double-entry method. Hard copy CRFs will be kept in locked filing cabinets accessible to only authorized investigators. The e-CRFs will be stored in an encrypted data format in the server using the Advanced Encryption Standard, with access restricted to only authorized investigators. Data confidentiality will be guaranteed by minimizing the number of personnel handling the data.

#### Quality assurance

A Data Monitoring Committee (DMC) has been established. The DMC consists of an independent director from the Clinical Research Management Office of Shandong University of TCM, an independent director from the reproductive center of the affiliated hospital of Shandong University of TCM, and an independent director from the school of Information Management of Shandong University of TCM. DMC will be responsible for data monitoring, interim analysis, assessment of post-intervention adverse events and handling cases of liver and kidney dysfunction, review of core trial procedures and documentation, discussion of any revisions to the main study protocol, and making the final decision to terminate the trial.

#### Data dissemination

Study results will be disseminated in Open Access, peer-reviewed journals and shared through oral and poster presentations at international conferences. All resources (research summaries, training tools, manuals, etc.) will be uploaded to an online knowledge management platform.

#### Data analysis

Statistical analyses will be performed using SPSS software version 26.0 (IBM Corp, Armonk, NY). Kolmogorov-Smirnov test will be used to test the normality of the data. Normally distributed continuous variables are reported as mean ± SD, while non-normally distributed continuous variables are reported as median and IQR. Categorical variables are reported as absolute and relative percentage frequencies. For comparison of the baseline characteristics and outcomes, independent Student’s *t* test or the Mann-Whitney *U* test are used to evaluate the mean or median differences between the placebo and DKP groups for normally distributed continuous variables, and the Pearson *χ*^2^ test for categorical variables.

Multiple imputation will be used to process missing values in the data of this study. The intention-to-treat analysis is used to examine the differences in the clinical pregnancy rate for the two treatment arms in the primary analysis using the Pearson *χ*^2^ test. Similarly, the multivariate regression model is used to adjust the results based on potential confounding factors. All the tests are two-tailed, and the significance level is set as *p* < 0.05.

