### Eligibility criteria

#### Inclusion criteria

Participants ≥ 35 years with poor pre-stimulation ovarian reserve parameters (AFC < 5, AMH < 1.2 ng/mL) and with an expected poor ovarian response (fewer than four oocytes) after standard ovarian stimulation will be recruited in this study.

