#### Secondary outcomes

Secondary outcomes include total retrieved oocyte count, embryo quality, endometrial thickness on ET day, implantation rate, early miscarriage rate, and safety assessment on the TCM formula. Early miscarriage is defined as the spontaneous loss of pregnancy within the first 13 weeks of gestation. Implantation rate is defined as the number of gestational sacs per the number of embryos transferred.

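### The normality pre-test commits the oocyte count to medians, which move mostly in whole-oocyte steps and estimate a modest gain poorly

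*Protocol article*

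**What the plan says.** Under Data analysis, the article states that a "Kolmogorov-Smirnov test will be used to test the normality of the data". Variables that pass are given as mean and SD; "non-normally distributed continuous variables are reported as median and IQR". The next sentence names the t test and the Mann-Whitney test together and says that they "are used to evaluate the mean or median differences between the placebo and DKP groups for normally distributed continuous variables". Read literally, both tests belong to normal data and no test is assigned to non-normal data. The evident intent is t test if normal, Mann-Whitney if not.

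Secondary outcomes lists "total retrieved oocyte count" first. Inclusion criteria restricts entry to women "with an expected poor ovarian response (fewer than four oocytes) after standard ovarian stimulation".

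For the primary outcome, Data analysis plans a Pearson chi-square test by intention to treat. It then mentions a multivariate regression to adjust for possible confounders, without naming outcomes or covariates. No effect measure is fixed for the oocyte count.

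**The concern.** A normality test on the outcome chooses how the treatment effect is expressed. For a count of around two to four in over 200 women per arm, the answer is known before any data arrive: an integer variable with so few values cannot pass. The rule therefore commits this outcome to medians, although it reads as a data-driven choice.

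The median of a small count can move only in whole steps, or half steps when the number per arm is even. A modest true gain is then likely to appear as no difference or as a full oocyte, and which of these appears depends heavily on where the placebo distribution sits relative to the integers. The article's background and discussion both name low oocyte yield as part of the problem in these women, so readers will want to know the size of any gain.

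**Working it through.** **Inputs from the article.** 203 evaluable and 230 recruited per arm (Sample size calculation); two-sided 0.05; fewer than four oocytes expected.

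**Assumptions.** The article gives no oocyte mean, SD or target gain. I assume Poisson counts, placebo means from 2 to 5 and a true gain of 0.5. Over-dispersed counts (variance 1.5 times the mean) and under-dispersed counts (about 0.6 times the mean) were also tried.

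**1. The plan's own figure.** For 0.40 against 0.25 with pooled variance and 90% power:

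n = [1.960·√(2·0.325·0.675) + 1.2816·√(0.25·0.75 + 0.40·0.60)]² / 0.15² = (1.298 + 0.838)² / 0.0225 ≈ 202.8, so 203 per arm.

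This agrees with the article. It concerns the primary outcome; no figure is given for oocytes.

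**2. The pre-test.** For a Poisson mean of 3, P(X ≤ 3) = 0.647, while a normal distribution with the same mean and variance gives 0.500 at 3. The Kolmogorov-Smirnov distance is therefore about 0.147. The uncorrected 5% critical value is about 1.358/√n, which is 0.090 at n = 230 and 0.095 at n = 203. In simulation (400 trials per scenario, 230 per arm), normality was rejected in 100% of trials in all 18 scenarios (three distributions, six placebo means from 2 to 5), with and without the Lilliefors correction.

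**3. Difference in medians, exact calculation at 203 per arm.** The sample median is at most k when at least 102 of 203 counts are at most k, so

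P(median ≤ k) = P(Bin(203, P(X ≤ k)) ≥ 102).

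- Mean 2: P(X ≤ 1) = 0.406, so the median is 2 with probability 0.997.
- Mean 2.5: P(X ≤ 2) = 0.544, so the median is 2 with probability 0.895, otherwise 3.
- Mean 3: P(X ≤ 2) = 0.423, so the median is 3 with probability 0.986.
- Mean 3.5: P(X ≤ 3) = 0.537, so the median is 3 with probability 0.852, otherwise 4.
- Mean 4: P(X ≤ 3) = 0.434, so the median is 4 with probability 0.972.

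The main products, for a true gain of 0.5:

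| Placebo → DKP mean | Most likely median difference | Probability |
|---|---|---|
| 2 → 2.5 | 0 | 0.997 × 0.895 ≈ 0.89 |
| 2.5 → 3 | 1 | 0.895 × 0.986 ≈ 0.88 |
| 3 → 3.5 | 0 | 0.986 × 0.852 ≈ 0.84 |
| 3.5 → 4 | 1 | 0.852 × 0.972 ≈ 0.83 |

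Simulation at 230 per arm agrees within simulation error: 0 in 91% and 84% (means 2 and 3), 1 in 91% and 82% (means 2.5 and 3.5).

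**4. Between these points.** At a placebo mean of 2.7 and 230 per arm, the difference is 0 in about 55% of trials and 1 in about 40%. With an even number per arm, a difference of 0.5 appears in about 2 to 5% of Poisson trials.

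**5. No true effect.** With a mean of 2.7 in both arms, medians differ by a whole oocyte in about 45% of trials at 230 per arm. At 203 per arm, P(X ≤ 2) = 0.494 gives a median of 2 with probability 0.428, hence 2 × 0.428 × 0.572 ≈ 0.49.

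**6. Difference in means.** It averages 0.50 in these Poisson settings. Its standard error at placebo mean 3 and 230 per arm is √((3 + 3.5)/230) ≈ 0.17.

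**7. Power and an alternative estimate.** At Poisson mean 3, power was 85% for the t test and 83% for Mann-Whitney; over-dispersed, about 70% for both. A Hodges-Lehmann shift was also always 0 or 1, split roughly evenly, so adding it to Mann-Whitney does not help.

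**The case against.** The strongest reply is that inference is barely affected. Because the pre-test rejects every time, the test is in effect fixed for this outcome, so there is no data-driven switching to distort error rates. Mann-Whitney power stays within about 3 points of the t test, and median with IQR is a conventional summary for skewed counts. All of this stands, and it confines the point to the effect estimate.

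Second, the 0.5 gain is assumed. With a gain of 1.0 at 230 per arm, the median difference is exactly 1 in 96 to 100% of trials at placebo means 2, 2.25, 3 and 3.25, and in 55 to 78% at 2.5, 2.75 and 3.5. A result of zero or double the truth is therefore particular to gains near a half. The coarseness is more general: at placebo mean 2.5, gains of 0.25 and of 1.0 both most often gave 1 (63% and 76%).

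A reader might also infer more than the article supports:

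- **That the result is always 0 or 1, set only by the placebo mean.** Half-oocyte differences occur with even numbers per arm, and at intermediate means sampling variation decides.
- **That a rank test leaves no adjusted analysis.** Data analysis already mentions a multivariate regression. Its scope is unclear, but it is not limited to pregnancy.
- **That the oocyte count is the designated mechanistic support for a pregnancy effect.** The article lists it among several secondary outcomes and gives it no such role.
- **That endometrial thickness is equally affected.** It is a measurement in mm, and the integer argument does not carry over.

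**Conclusion.** The point holds as a free improvement to one secondary outcome. The pre-test is a stated rule, not a detail left to another document, and for this outcome its result is settled in advance under every distribution tried. The median difference is then a poor guide to the size of the gain. At an assumed gain of 0.5 it most often shows 0 or 1 according to the placebo mean, and with no effect at all it can show a whole oocyte in nearly half of trials when the mean lies near 2.7. The exact percentages rest on the Poisson and half-oocyte assumptions; that medians of small integers move in steps does not.

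The pregnancy analysis is unaffected. It would be wrong to conclude that the trial loses meaningful power or that its error rates are at risk.

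**What to change.** For the oocyte count, drop the normality pre-test and pre-specify the difference in means with a 95% CI, from a Welch t test or a linear model with robust standard errors. Keep Mann-Whitney as a sensitivity analysis; medians and IQR can remain as description.

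Reword the comparison sentence so that it no longer assigns both tests to normally distributed variables.

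The regression already mentioned can supply an estimate adjusted for pre-treatment AFC, AMH and age. Any gain in precision depends on correlations that the article does not give, and may be smaller because eligibility restricts AFC and AMH.

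The cost is analysis wording only: no extra participants, visits or data.

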### Trial design and setting

This is a prospective, multi-center, randomized, double-blinded, placebo-controlled, superiority study. Eligible participants will be randomly assigned to the experimental group (DKP) or the control group with a 1:1 ratio. The participants will be recruited from 12 hospitals across mainland China. The study flow chart and schedule are shown in Fig. 1 and Table 1 (SPIRIT Figure), respectively.

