##### Oocyte retrieval and embryo culture

BD Falcon IVF medium (Becton, Dickinson and Company, Franklin Lakes, NJ, USA) will be used to collect the Oocytes and perform embryo culture. Incubation conditions will be set at 6% CO_2_, 5% O_2_, and 37.0 °C (C200 CO_2_ Incubator, Labotect Labor-Technik-Göttingen GmbH, Göttingen, Germany). Culture oocytes will be inseminated for IVF or decumulated for ICSI.

Transfer of two high-quality embryos will be performed on day 3, and the surplus frozen on day 3 or day 5 based on the routine at different sites. All good quality embryos will be cryopreserved via vitrification (CBS-ViT-HS, CryoBioSystem®, L’Aigle, France). Dimethylsulfoxide and ethylene glycol will be used as cryoprotectants (Irvine Scientific Freeze Kit®, Irvine Scientific, Newtown Mount Kennedy, Ireland, and Vitrification Kit 101, Cryotech®, Tokyo, Japan).

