### Outcome measurements

#### Primary outcomes

The primary outcome is the ongoing clinical pregnancy rate, defined as the presence of intrauterine gestation sac with fetal heart rate at 7 weeks of gestation.

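### The primary Pearson test is valid but ignores centre, age, AFC and AMH, and the adjusted model beside it names no covariates; one pre-specified model would serve better

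*Protocol article*

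**What the plan says.** Under Primary outcomes the endpoint is binary: "The primary outcome is the ongoing clinical pregnancy rate", assessed at 7 weeks of gestation.

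Under Data analysis, "The intention-to-treat analysis is used to examine the differences in the clinical pregnancy rate for the two treatment arms in the primary analysis", by the Pearson chi-square test. The next sentence adds that "the multivariate regression model is used to adjust the results based on potential confounding factors". No covariate is listed and no type of model is given. The preceding paragraph of that section gives t, Mann-Whitney and Pearson tests "For comparison of the baseline characteristics and outcomes".

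On setting, "The participants will be recruited from 12 hospitals across mainland China". Eligibility requires age of at least 35 and below 45, AFC below 5 and AMH below 1.2 ng/mL. The Discussion says that women of this age with reserve this low are more likely to do poorly in IVF.

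Table 1 places the basic ovarian reserve test (AFC, basal FSH, AMH) in the post-allocation column for weeks 1–6, the same column as study treatment.

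**The concern.** Centre, age, AFC and AMH are the obvious candidates to predict pregnancy in this population. The first costs nothing to record, and the other three must be known before enrolment. A primary test that uses none of them gives up whatever precision they carry.

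The wording of the adjusted analysis is a second weakness. In a randomised comparison, covariates are chosen in advance because they predict outcome, not because they are suspected confounders. With no list, covariates could be picked after the data are seen, for instance because a baseline test happened to be significant. The adjusted result would then be hard to interpret.

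Third, Table 1 suggests that on-treatment AFC and AMH values may exist beside the eligibility values. Adjusting for a value measured after treatment began could distort the treatment effect, and an unspecified covariate list does not rule that out.

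**Working it through.** **1. The plan's own figure.** Inputs from Sample size calculation: 0.40 v 0.25, two-sided 0.05, 90% power, pooled variance, 1:1.

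n per group = [1.960·√(2·0.325·0.675) + 1.2816·√(0.40·0.60 + 0.25·0.75)]² / 0.15²
= [1.960·0.6624 + 1.2816·0.6538]² / 0.0225
= (2.136)² / 0.0225 = 202.8, so 203 per group and 406 in total.

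This matches the plan exactly. Allowing for 10% dropout, 406/0.9 gives 452 after rounding up; the plan recruits 460. The trial therefore has its planned power with no adjustment.

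**2. What adjustment could add, by approximation.** The documents give no prognostic strength. Let R² be the assumed share of outcome variance explained by centre, age, AFC and AMH. The variance scales by (1 − R²), so the effective size is 203/(1 − R²) per group, and the number needed for 90% power is 203·(1 − R²).

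| Assumed R² | Effective n per group | Power | n per group for 90% |
|---|---|---|---|
| 0 | 203 | 90.0% | 203 |
| 0.02 | 207 | 90.6% | 199 |
| 0.05 | 214 | 91.4% | 193 |
| 0.10 | 226 | 92.8% | 183 |
| 0.15 | 239 | 94.1% | 173 |

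**3. The same question by simulation.** 406 women, 12 centres, three covariates; Pearson test against the treatment test in a logistic model with centre terms and covariates; 2,000 runs per setting. The standard deviations (SD) are on the log-odds scale and are assumptions.

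| Centre SD | Covariate SD | R² | Pearson | Adjusted | Difference (points) |
|---|---|---|---|---|---|
| 0 | 0 | 0 | 90.1% | 90.6% | +0.5 |
| 0.3 | 0.3 | 0.04 | 89.6% | 90.3% | +0.7 |
| 0.3 | 0.5 | 0.07 | 89.8% | 91.7% | +1.9 |
| 0.5 | 0.5 | 0.09 | 90.4% | 92.5% | +2.1 |
| 0.5 | 0.8 | 0.15 | 91.1% | 93.7% | +2.6 |

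A separate set of 2,500 runs per setting, with covariate SD 0.7, gave 90.1% v 91.8% (centre SD 0.3) and 90.4% v 93.2% (centre SD 0.5). With nothing prognostic it gave 88.8% v 88.2%, a loss of 0.6 points. A third simulation found about no gain at covariate SD 0.4 with centre SD 0.2, and a loss of about 0.3 points with nothing prognostic.

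**4. Type I error.** In the simulations of step 3, Pearson rejected a true null in 4.6% and 5.5% of runs, and the adjusted likelihood-ratio test in 5.8% in both settings (Monte Carlo error about 0.5 points). The other two simulations put the adjusted test at 5.1% and at 4.9–6.0%. Slight inflation with 12 centre terms cannot be excluded.

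**5. What an open covariate list allows.** Null simulation, 3,000 runs, covariate SD 0.7, centre SD 0.4. Pearson alone and the full adjusted model alone each rejected in 5.6%. Taking whichever of the two is significant gave 7.4%. Taking the best of Pearson and every covariate subset gave 10.2%. These are worst cases under deliberate selection, not a forecast of what this team will do.

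**The case against.** The strongest reply is that nothing here is wrong. The article states which analysis is primary, the Pearson test is valid, and it matches the test used for sizing. A regression is planned as well, and an exact covariate list commonly sits in a statistical analysis plan, which is not shown. Eligibility truncates age, AFC and AMH, so the lower rows of assumed strength are the more plausible. A covariate SD of 0.7 already means about six-fold odds between the 10th and 90th percentiles (exp(0.7 × 2.56) = 6.0). All of this stands. It limits the point to a cheap improvement in the stated primary method, not the repair of a fault.

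Four stronger readings are tempting and not supported.

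- **Unstratified allocation.** A reader might infer this from "Patients will be randomly divided into two groups (1:1 ratio) using computer-generated random numbers". The section mentions neither strata nor blocks, but a condensed article that is silent has not said there are none.
- **Site-specific gonadotropin dosing.** The COH section sets dose by the individual patient. The phrase "based on the routine at different sites" concerns only whether surplus embryos are frozen on day 3 or day 5, so it says little about the size of any centre effect.
- **Site imbalance as bias.** With 460/12, about 38 women per site, the chance that at least one site splits 25:13 or worse is 1 − (1 − 0.073)¹² = 0.60. That assumes simple randomisation and equal sites, neither of which is stated. Chance imbalance is also already covered by the test's error rate. One such site with a pregnancy rate 10 points off average would move the difference by about 12/230 × 0.10 = 0.5 points, against a 15-point target.
- **Baseline tests as the covariate selector.** The article does not say this. The wording only leaves it open.

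**Conclusion.** The point holds as a modest improvement. The Pearson test keeps its nominal error rate and the planned 90% power, so the trial's conclusion is not at risk from it. Using centre, age, AFC and AMH would raise simulated power by about nil to 3 points. The variance approximation gives up to 4 points, at R² = 0.15. In sample size, R² of 0.02 to 0.15 corresponds to 2–15% fewer patients for the same power. Every one of these figures rests on assumed prognostic strength.

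The gain in pre-specification does not depend on those assumptions. Naming one model, its covariates and its rank closes the route by which selective reporting could lift a 5% error rate to about 7–10% in the worst case, and it keeps on-treatment ovarian reserve values out of the adjustment.

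**What to change.** Before outcomes accrue, and before any interim look by the Data Monitoring Committee, state the following.

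- **Primary analysis:** logistic regression of ongoing clinical pregnancy on arm, centre, age, AFC and AMH. Pool small centres by a rule fixed in advance, or use a random intercept for centre.
- **Covariate values:** only those measured before randomisation. Clarify the timing of the ovarian reserve test in Table 1.
- **Reporting:** the standardised risk difference with 95% CI, and the odds ratio. Keep the Pearson test as supportive.
- **Selection:** no covariate is added or dropped because of a baseline significance test.
- **Randomisation:** say whether it is stratified; if so, put the strata in the model. The allocation scheme itself need not change.

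The cost is a paragraph of wording, handled under Protocol amendments where that section requires it, and no new data. The downsides are a loss of up to about half a power point if nothing is prognostic, possible slight small-sample inflation of the adjusted test with 12 centre terms, and the extra standardisation step, since the model's odds ratio is conditional on the covariates.
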